## Abstract

Background: Coronary artery bypass grafting (CABG) is a well-established revascularization strategy for patients with multivessel coronary artery disease. The effectiveness of CABG is significantly influenced by antiplatelet therapy aimed at maintaining graft patency and reducing thrombotic complications. However, substantial inter-individual variability exists in platelet function responses to standard therapies such as aspirin and clopidogrel, leading to antiplatelet resistance. This variability has been linked to increased risks of myocardial infarction, stroke, and early graft failure. Platelet function testing (PFT) offers a potential strategy to identify resistance and guide more personalized antiplatelet therapy. This study aims to evaluate the association between perioperative platelet function test results and clinical outcomes following CABG. By assessing platelet responsiveness at multiple timepoints and correlating findings with postoperative events, the study seeks to determine whether PFT can stratify risk and improve patient management. Methods: This is a prospective, single-centre, observational cohort study conducted at a tertiary NHS cardiac surgery centre. Patients having elective or urgent isolated CABG will be enrolled and undergo perioperative PFT using the TEG6s system. Clinical outcomes will be monitored for 12 months postoperatively, with primary endpoints assessing the correlation between platelet function results and major adverse cardiovascular and cerebrovascular events (MACCE). Secondary endpoints will include the prevalence of antiplatelet resistance, demographic predictors, and the feasibility of integrating PFT into clinical workflows. Results: This study will report the prevalence of aspirin and clopidogrel resistance in CABG patients based on TEG6s PFT, as well as the correlation between platelet function results and MACCE, postoperative bleeding, and the need for surgical re-exploration. Additionally, it will examine the associations between demographic and clinical factors—such as diabetes status, renal function, BMI, and surgical technique—and variability in platelet responsiveness. The feasibility of incorporating PFT into perioperative workflows will also be evaluated, assessing whether results could support personalized antiplatelet management in future clinical trials. Conclusions: Findings from this study will provide real-world evidence regarding platelet function variability in CABG patients and suggest that PFT may identify those at increased risk of thrombotic complications. This exploratory analysis supports the need for larger interventional trials aimed at optimizing individualized postoperative antiplatelet therapy to improve surgical outcomes.

## 1. Introduction

Coronary artery disease remains one of the leading causes of morbidity and mortality worldwide, despite advancements in medical and interventional therapies [1]. Coronary artery bypass grafting (CABG) is a well-established surgical approach for patients with multivessel or complex coronary artery disease, offering durable revascularization and improved long-term outcomes compared to percutaneous coronary intervention in select patient populations [2]. However, the success of CABG is contingent on maintaining graft patency and minimizing postoperative thrombotic complications, which are heavily influenced by perioperative antiplatelet therapy [3].

Aspirin and clopidogrel, the most commonly prescribed antiplatelet agents in coronary artery bypass grafting patients, exert their effects by irreversibly inhibiting platelet cyclooxygenase-1 and P2Y12 receptors, respectively. Despite their widespread use, there is mounting evidence of substantial inter-individual variability in response to these agents, a phenomenon referred to as antiplatelet resistance [4]. Meta-analytic data suggest that aspirin resistance may affect up to 38 percent of patients, while clopidogrel resistance has been observed in up to 40 percent of coronary artery bypass grafting recipients [5]. This variability in platelet responsiveness has been linked to an increased risk of adverse cardiovascular events, including myocardial infarction, stroke, and early graft failure [6].

Platelet function testing (PFT) offers a potential strategy for identifying patients with antiplatelet resistance and guiding personalized therapy to mitigate thrombotic risk. Technologies such as light transmission aggregometry, VerifyNow, impedance aggregometry, and thromboelastography allow for real-time assessment of platelet reactivity, thereby providing objective measures of antiplatelet efficacy [7]. However, despite the technological feasibility, routine use of PFT in CABG pathways remains limited due to the lack of prospective, outcome-based evidence supporting its clinical utility.

Current international guidelines do not offer specific recommendations on personalized antiplatelet strategies post-coronary artery bypass grafting, in part due to this evidence gap [2]. A recent UK-wide survey of cardiac surgeons found significant variability in antiplatelet prescribing practices, reinforcing the need for robust data to inform clinical decision-making in surgical patients [8].

This observational study seeks to address the unmet need for robust data linking perioperative platelet function test (PFT) results with clinical outcomes following CABG. The primary objective of this study is to determine the association between perioperative platelet function test results and clinical outcomes, including major adverse cardiovascular and cerebrovascular events (MACCE), postoperative bleeding, and the need for surgical re-exploration. In this study, MACCE is defined as a composite of myocardial infarction, non-fatal stroke, and cardiovascular death, assessed at 30 days and one year following CABG. The secondary objectives include assessing the prevalence of aspirin and clopidogrel resistance in CABG patients using platelet mapping, identifying demographic and clinical predictors of antiplatelet resistance—such as age, sex, diabetes, renal function, ethnicity, BMI, and surgical technique—and evaluating temporal trends in platelet responsiveness from the preoperative baseline through early and late postoperative periods. Additionally, the study will explore the relationship between high platelet reactivity and the need for postoperative escalation of care, including ICU readmission, inotropic support, and transfusions. Lastly, it will assess the feasibility of integrating PFT into the perioperative care pathway to support individualized antiplatelet management in future interventional studies.

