#### 2.1.1. Overall Design

The study will be conducted at a single tertiary NHS cardiac surgery centre, enrolling 100 patients who will receive standard perioperative and postoperative care according to institutional and national guidelines. No study drug or investigational device will be tested. The study aims to generate real-world data that may inform future interventional trials or guideline updates regarding the role of PFT in optimizing antiplatelet therapy for surgical patients.

A formal sample size calculation was performed to ensure sufficient statistical power to detect meaningful variability in platelet function and its association with clinical outcomes. Assuming a moderate effect size (Cohen’s d = 0.5), a two-sided alpha level of 0.05, and 80% statistical power, the minimum required sample size for comparison of platelet function measures was estimated at 63 patients.

To account for an anticipated attrition rate of approximately 20%, due to loss to follow-up or incomplete PFT across multiple perioperative timepoints, the adjusted minimum sample size was calculated to be approximately 80 patients. To further enhance robustness and allow for exploratory subgroup and longitudinal analyses, a final target sample size of 100 patients was selected.

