#### 2.5.3. Clinical Outcomes and Follow-Up

Participants will be followed from preoperative baseline through twelve months postoperatively, capturing routine clinical outcomes including:Major adverse cardiovascular and cerebrovascular events, including myocardial infarction, stroke, and cardiovascular deathPostoperative bleeding, defined as Bleeding Academic Research Consortium type two or higherNeed for surgical re-exploration for haemostasisTransfusion requirements, including blood product administrationDuration of hospital stay, including intensive care unit and ward admissionWound healing and postoperative complications

Follow-up visits will occur at discharge between postoperative day five and seven, at six weeks postoperatively, at thirty days via telephone contact, and at twelve months through digital health records review.

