#### 2.7.3. Handling of Missing Data

Primary analyses will follow a complete case approach. If more than 10% of data is missing for a key variable, multiple imputation may be considered. All missing data patterns will be documented, and deviations will be reported in the final analysis.

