#### 2.7.4. Primary Endpoint Analysis

The primary objective of this study is to evaluate the association between platelet function test results and clinical outcomes in patients undergoing elective and urgent CABG.

Summary Measures

Platelet function results will be summarized as mean ± standard deviation or median with interquartile range (IQR), depending on data distribution, for:AA channel (aspirin response)ADP channel (clopidogrel response)

Clinical outcomes, including MACCE, bleeding, re-exploration, and transfusion, will be reported as frequencies and proportions.

Method of Analysis

Correlation analysis: Pearson’s correlation for normally distributed data, Spearman’s rank correlation for non-parametric dataLogistic regressionEstimates the odds of postoperative events based on platelet resistance status (resistant vs. non-resistant)Adjusts for potential confounders (age, diabetes, renal function, surgical factors)Hierarchical data structure: Generalized estimating equations (GEE) or mixed-effects models will be used to account for repeated measures of platelet function over time.

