#### 2.7.7. Intention-to-Treat Statement

Since this is a non-randomized observational study, an intention-to-treat analysis is not applicable. Analyses will be conducted on participants with complete platelet function and outcome data.

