### 3.2. Platelet Function and Clinical Outcomes

Platelet function test results will be analyzed at three timepoints: preoperative baseline, postoperative discharge, and six-week follow-up. The degree of platelet inhibition will be reported as percentage inhibition in response to arachidonic acid and adenosine diphosphate pathways, reflecting aspirin and clopidogrel effectiveness, respectively.

The prevalence of aspirin and clopidogrel resistance in the study population will be determined based on predefined cutoff values from the TEG6s Platelet Mapping system. Differences in platelet responsiveness between groups will be evaluated using repeated measures analysis of variance or non-parametric alternatives, depending on data distribution.

The primary analysis will assess correlations between platelet function test results and major adverse cardiovascular and cerebrovascular events, including myocardial infarction, stroke, cardiovascular death, postoperative bleeding complications, and the need for surgical re-exploration. Univariate correlations will be explored using Pearson or Spearman correlation coefficients, while logistic regression models will estimate the odds ratios for adverse outcomes associated with platelet resistance.

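### One-year MACCE is analysed as yes/no in complete cases although 12-month losses are foreseen: depending on the unstated rule for lost patients, the proportion is overstated or observed events are discarded

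*Protocol article*

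**What the plan says.** All references are to the Protocol article.

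- **Outcome and horizon.** "MACCE is defined as a composite of myocardial infarction, non-fatal stroke, and cardiovascular death, assessed at 30 days and one year following CABG" (1. Introduction). MACCE is part of the primary objective. Twelve-month follow-up is "at twelve months through digital health records review" (2.5.3).
- **Summary and model.** "Clinical outcomes, including MACCE, bleeding, re-exploration, and transfusion, will be reported as frequencies and proportions" (2.7.4). For the association, "logistic regression models will estimate the odds ratios for adverse outcomes associated with platelet resistance" (3.2; 2.7.4 says the same in other words). No time-to-event method or censoring rule appears.
- **Analysis set.** "Analyses will be conducted on participants with complete platelet function and outcome data" (2.7.7).
- **Missing data.** "Primary analyses will follow a complete case approach", and "If more than 10% of data is missing for a key variable, multiple imputation may be considered" (2.7.3; 2.7.5 repeats both).
- **Expected loss.** The sample size is inflated "To account for an anticipated attrition rate of approximately 20%, due to loss to follow-up or incomplete PFT across multiple perioperative timepoints" (2.1.1). Section 2.7.2 lists the numbers lost at six weeks and at 12 months among the items to be reported.

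**The concern.** A yes/no outcome at one year is fully known only for a patient who has had the event or who has been followed event-free for the whole year. A patient lost at, say, five months fits one of two rules, and the article does not choose between them.

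- **Rule A.** An event seen before loss makes the outcome known, so that patient stays; a patient event-free when lost has an unknown outcome and leaves. The denominator loses only event-free patients, so the one-year proportion is too high even when loss is random.
- **Rule B.** Everyone without a 12-month record leaves. The proportion is then unbiased under random loss, but events already observed are discarded.

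The requirement for complete platelet data adds to this. If it means all three tests in 2.5.1, a patient who dies or withdraws before the six-week test is excluded together with any early event, however complete the records are.

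At stake are the one-year event proportion and, in a cohort of 100, some of what may be only about ten events.

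**Working it through.** **The plan's own figure.** The only number on loss is the inflation from 63: 63 / (1 − 0.20) = 78.75, rounded up to 79. This agrees with the stated figure of approximately 80. The 20% combines loss to follow-up with incomplete platelet testing, and the 12-month share is not given.

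**Inputs.**
- N = 100 (2.1.1).
- One-year MACCE risk p = 10%: assumed, as none is stated.
- Loss by 12 months L = 5%, 10% or 20%: assumed.
- Loss independent of MACCE: assumed.
- Event timing: constant hazard over the year, or half of the event hazard in the first 30 days: assumed.

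**Formulas.** With constant hazards, h = −ln(1 − p) and λ = −ln(1 − L).
- Events seen before loss: E = N × h/(h + λ) × [1 − (1 − p)(1 − L)]
- Event-free with full follow-up: F = N(1 − p)(1 − L)
- Rule A proportion: E/(E + F)
- Rule B: N(1 − L) patients and Np(1 − L) events; observed events dropped = E − Np(1 − L)

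**Worked case, L = 20%, constant hazard.** h = 0.1054 and λ = 0.2231. E = 100 × 0.3207 × 0.28 = 8.98. F = 100 × 0.9 × 0.8 = 72. Rule A: 8.98/80.98 = 11.1%. Rule B: 8.0 events in 80 patients = 10%, with 8.98 − 8.00 = 0.98 observed events dropped.

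| Loss | Event timing | E | F | Rule A | Rule B events | Observed events dropped |
|---|---|---|---|---|---|---|
| 5% | constant | 9.75 | 85.5 | 10.2% | 9.5 | 0.25 |
| 5% | half early | 9.86 | 85.5 | 10.3% | 9.5 | 0.36 |
| 10% | constant | 9.50 | 81 | 10.5% | 9.0 | 0.50 |
| 10% | half early | 9.71 | 81 | 10.7% | 9.0 | 0.71 |
| 20% | constant | 8.98 | 72 | 11.1% | 8.0 | 0.98 |
| 20% | half early | 9.41 | 72 | 11.6% | 8.0 | 1.41 |

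**Second loss model.** Losses are uniform between six weeks and 12 months, with 30–70% of events in the first 30 days. Rule A gives 10.3–10.4% at 5% loss, 10.7–10.9% at 10% and 11.4–11.9% at 20%. At 20% loss, rule B keeps 8.0 of 9.3–9.7 observed events, so 1.3–1.7 are dropped.

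**Other risks.** Over p = 5% to 15% and L = 5% to 20% in the first loss model, rule A overstates by 2% to 17% in relative terms, and rule B drops 0.1 to 2.1 observed events.

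**Comparator.** Under independent loss, a cumulative incidence estimate with censoring returns the assumed risk and uses every event in E.

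**Odds ratio.** Under rule A with no true association (second loss model), equal 20% loss gives 1.00. Loss of 25% against 10% by resistance status gives about 1.15 (half of events early), and 30% against 10% gives about 1.24 (70% early). Both gaps are assumptions.

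**The case against.** **The 20% is not a 12-month MACCE loss rate.** This stands. It includes incomplete platelet testing and inflates a sample size for comparing platelet measures. One-year outcomes come from records, so a missed visit need not lose the outcome and true loss may be far lower. At 5% loss the effect is small.

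**Upward bias and discarded events cannot both be charged to the plan.** This stands. A reader might infer that the reported proportion will be too high and that events will also be lost. Each belongs to a different rule, and the article fixes neither.

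**The odds ratio need not be biased.** This stands. A reader might infer a spurious association, but that needs rule A and unequal loss by resistance status, and the article gives no figure for such a gap. Even then, ln(1.15) to ln(1.24) is 0.14 to 0.22, against a standard error of √(1/4 + 1/36 + 1/6 + 1/54) = 0.68 for an assumed 4 events in 40 resistant and 6 in 60 non-resistant patients.

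**Non-cardiovascular death.** A reader might infer that logistic regression mishandles it. With known follow-up, coding such a death as no MACCE by one year gives exactly the one-year cumulative incidence, so this is no error in itself.

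**A fixed-horizon logistic model is accepted practice, 2.7.4 does not name the horizon, and details belong in the SAP.** This stands in part. But the article itself states the model, the summary and the analysis set, and offers no other method for the one-year outcome. Imputation above 10% missing softens the problem, but it is only optional and complete case stays primary.

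**Conclusion.** The point holds as a cheap improvement to the analysis, not as a demonstrated serious bias. The stated combination of a yes/no one-year outcome, a complete-data set and foreseen 12-month losses must either overstate the one-year proportion or discard observed events, for whatever share of patients is lost. At an assumed 10% risk, the cost is about 0.2 to 0.4 percentage points at 5% loss and 1.1 to 1.9 points at 20% loss under one rule, or about 0.3 to 1.7 observed events under the other. For comparison, the standard error of 10% in 100 patients is √(0.1 × 0.9/100) = 3 points. The size depends on the assumed risk, loss and event timing, and on loss being independent of MACCE. The documents do not support a claim that the odds ratio will be biased.

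**What to change.** In 2.7.4, with matching wording in 2.7.3 and 2.7.7:

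- Analyse one-year MACCE as time to first event. For the preoperative test, start at surgery and censor at the last record or 365 days.
- Include every patient who has the platelet test used in that model, rather than requiring all tests and a 12-month record.
- For the discharge or six-week test, use a landmark analysis of later events, as a supplementary analysis only. Starting the main analysis at the six-week test would exclude every earlier event and so discard more than the present plan does.
- Report one-year cumulative incidence with non-cardiovascular death as a competing event.
- Estimate the association with a Firth-penalised Cox model, since few events are likely.
- Keep logistic regression for in-hospital and 30-day outcomes.

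Cost: event and last-record dates must be taken from the records review already planned. The one-year result becomes a hazard ratio instead of an odds ratio, and proportional hazards must be checked. No extra patients or visits are needed.

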## 2. Methods

### 2.1. Study Design

This is a prospective, single-centre, observational cohort study designed to evaluate the association between perioperative platelet function and clinical outcomes in patients undergoing elective and urgent CABG. The primary objective is to assess variability in platelet responsiveness to standard antiplatelet therapy and its correlation with MACCE, postoperative bleeding, and the need for surgical re-exploration.

#### 2.1.1. Overall Design

The study will be conducted at a single tertiary NHS cardiac surgery centre, enrolling 100 patients who will receive standard perioperative and postoperative care according to institutional and national guidelines. No study drug or investigational device will be tested. The study aims to generate real-world data that may inform future interventional trials or guideline updates regarding the role of PFT in optimizing antiplatelet therapy for surgical patients.

A formal sample size calculation was performed to ensure sufficient statistical power to detect meaningful variability in platelet function and its association with clinical outcomes. Assuming a moderate effect size (Cohen’s d = 0.5), a two-sided alpha level of 0.05, and 80% statistical power, the minimum required sample size for comparison of platelet function measures was estimated at 63 patients.

To account for an anticipated attrition rate of approximately 20%, due to loss to follow-up or incomplete PFT across multiple perioperative timepoints, the adjusted minimum sample size was calculated to be approximately 80 patients. To further enhance robustness and allow for exploratory subgroup and longitudinal analyses, a final target sample size of 100 patients was selected.

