#### 2.7.8. Secondary Endpoint Analysis

Analyses of secondary endpoints are exploratory and hypothesis-generating, as the study is not powered for statistical significance in these measures. Findings will guide future studies.

Variability in Platelet Function

Objective: Assess inter-individual variability in platelet inhibition across timepoints.Analysis:
Continuous values (% inhibition) summarized at baseline, discharge, and 6 weeksRepeated measures ANOVA or Friedman test for within-patient changesBoxplots and line graphs used for visualization

Prevalence of Platelet Resistance

Objective: Determine the proportion of patients with inadequate platelet inhibition.Analysis:
Categorical resistance status reported for each timepoint with 95% confidence intervalsChanges in resistance status analyzed using McNemar’s test for paired categorical data

Demographic and Clinical Predictors of Platelet Function

Objective: Explore associations between patient characteristics and platelet responsiveness.Analysis:
Univariable and multivariable linear regression for continuous % inhibition outcomesConsidered variables: age, sex, BMI, renal function, diabetes, and number of graftsSelection guided by clinical relevance and statistical significance (*p* < 0.1)

Impact of Platelet Resistance on Clinical Decision-Making

Objective: Evaluate whether platelet resistance influences treatment decisions, including DAPT use and discharge timing.Analysis:
Comparisons of DAPT prescription rates between resistant and non-resistant patients using chi-square or Fisher’s exact testLogistic regression to explore predictors of treatment decisions if data allows

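### The minimum of 63 patients is a per-group size used as the cohort total, and the calculation has no input for the clinical outcomes for which it claims power

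*Protocol article*

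**What the plan says.** Section 2.1.1 (Overall Design) reports a formal calculation made "to ensure sufficient statistical power to detect meaningful variability in platelet function and its association with clinical outcomes". Its inputs are a Cohen's d of 0.5 and "a two-sided alpha level of 0.05, and 80% statistical power". The result is that "the minimum required sample size for comparison of platelet function measures was estimated at 63 patients". After an allowance of about 20% for attrition, "the adjusted minimum sample size was calculated to be approximately 80 patients", and the target is then raised to 100. The words per group do not appear. Section 2.1.2 describes one cohort of 100 with no control arm, so 100 is a total.

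The primary objective (Introduction, and Sections 2.1, 2.6.1 and 2.7.4) is the association of platelet function results with clinical outcomes: MACCE, bleeding and re-exploration. Section 2.7.4 analyses it by correlation and by adjusted logistic regression for "the odds of postoperative events based on platelet resistance status (resistant vs. non-resistant"). Section 2.7.7 restricts analyses to participants with complete platelet function and outcome data. Section 2.7.8 calls the secondary analyses exploratory, "as the study is not powered for statistical significance in these measures".

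**The concern.** The figure 63 is familiar: it is what the usual two-sample formula returns for each group at d = 0.5. Here it is carried forward as if it were the whole study. If the comparison is between patients, the design needs about twice that number for the power it states.

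The second problem is separate. The calculation is described as a comparison of platelet function measures, while the primary analysis models clinical events. Nothing in the inputs links the two, yet the section says that power for the association with outcomes is secured.

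What is at stake is how a null result is read. The Discussion and Future Directions intend the study to show whether platelet function testing can stratify risk and to prepare randomised trials. A reader who trusts the 80% would take a null finding as fairly strong evidence against an association, which this sample cannot supply.

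**Working it through.** **Inputs from Section 2.1.1.** d = 0.5; two-sided alpha 0.05 (z = 1.960); power 80% (z = 0.842); attrition 20%; target 100 in total.

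**1. Reproducing 63.** For two independent groups of equal size:

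n per group = 2(1.960 + 0.842)² / 0.5² = 62.8, rounded up to 63.

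The exact t-test gives 63.8, so 64. The totals are 126 and 128. The stated figure reproduces exactly, as a per-group size.

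**2. Reproducing 80.** 63 / (1 − 0.20) = 78.75, or about 80. The attrition step is done correctly, but on the wrong base. From the total it would be 126 / 0.8 = 157.5, so 158 (128 / 0.8 = 160 by t-test).

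**3. Between-patient power at d = 0.5, even split (the best case), exact two-sample t-test.**

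| Evaluable patients in total | Power at d = 0.5 |
|---|---|
| 63 | 50% |
| 80 (100 less 20%) | 60% |
| 100 (no attrition) | 70% |

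With 80 evaluable patients split evenly, 80% power is reached at d = 0.63. As a check by the normal approximation: (1.960 + 0.842) / √(80/4) = 2.802 / 4.472 = 0.63.

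**4. Unequal split.** If the groups are patients with and without an event, the split is uneven. The documents give no event rate, so the rates below are assumptions. With 80 evaluable patients:

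| Assumed event share | Events / non-events | Power at d = 0.5 | d detectable with 80% power |
|---|---|---|---|
| 5% | 4 / 76 | 16% | 1.46 |
| 10% | 8 / 72 | 26% | 1.06 |
| 15% | 12 / 68 | 35% | 0.89 |

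**5. Within-patient reading.** If d is standardised by the SD of the within-patient differences, a paired or one-sample test needs 34 patients (33.4 rounded up), not 63. If d is standardised by the raw SD, with correlation ρ between timepoints:

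n = 2(1 − ρ)(1.960 + 0.842)² / 0.5²

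This gives 62.8, so 63 patients, at ρ = 0; 44 at ρ = 0.3; and 32 at ρ = 0.5. A total of 63 therefore follows only if repeated measurements on the same patient are taken to be uncorrelated.

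**6. Link to the primary outcomes.** An association with events, by correlation or by logistic regression on resistance status, would need at least an expected correlation, or an event rate with an odds ratio and a resistant share. Section 2.1.1 uses none of these.

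**The case against.** The strongest defence is that the calculation may concern change within patients. The wording about platelet function measures, the mention of incomplete tests across timepoints, the absence of a control arm and the repeated-measures analyses in Section 2.7.8 all leave room for that. On that reading 63 patients give 79% power even at ρ = 0, and 91% at ρ = 0.3. This part stands: it would be too strong to say that no reading yields 63, or that the study lacks 80% power for every comparison of platelet function. But the article states neither this test nor the zero correlation needed to arrive at 63, and a within-patient comparison does not bear on the association with outcomes, for which the section also claims power.

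A reader might also put the literature resistance figures from the Introduction (up to 38% and up to 40%) into the calculation and quote power for resistant versus non-resistant patients. The documents do not support that. Section 3.2 defines resistance by cutoffs on the platelet function test itself, so comparing mean platelet function between those two groups is circular, and no such comparison is planned. The percentages are also upper bounds from cited work, not planning values.

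Third, the study calls itself exploratory. The Abstract does so, and Section 2.7.9 stresses effect sizes and intervals. That softens the consequence. However, the statement in Section 2.7.8 about lacking power covers secondary endpoints, and Section 2.7.9 concerns multiplicity. Neither withdraws the formal power claim made for the primary objective.

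Finally, it would be wrong to call all the primary outcomes rare. They include bleeding of BARC type 2 or higher, and no rates are given. The event shares in the working are illustrations only.

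**Conclusion.** The point holds in two parts. First, for a comparison between two groups of patients, 63 is the size of one group, and the article uses it as the total. Power at d = 0.5 is then at most about 50% at 63, 60% at 80 evaluable and 70% at 100 evaluable, against the stated 80%. The rise to 100 does not absorb the error. These ceilings rest only on the article's own d and alpha and an even split. The lower range of 16% to 35% at 80 evaluable rests on assumed event shares of 5% to 15%.

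Second, whichever test was meant, the claim of sufficient power for the association with clinical outcomes is unsupported, because the calculation contains nothing about those outcomes.

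This does not show that 100 patients is the wrong number for an exploratory cohort. It shows that the stated justification does not deliver what it claims.

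**What to change.** Keep the target at 100 and correct Section 2.1.1:

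- State that 63 is the number per group for d = 0.5, so 126 in total (128 by t-test).
- Restate power at d = 0.5 as at most about 60% with 80 evaluable patients, with 80% power only from d of about 0.63 upward, both for an even split.
- If a within-patient comparison was intended, say so and give the correlation assumed.
- Delete the claim of sufficient power for the association with clinical outcomes. Label that association exploratory, reported by estimates and confidence intervals, in line with Section 2.7.9.

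A statement of the precision with which resistance prevalence will be estimated could be added, but it is optional: prevalence is a secondary endpoint and cannot stand in for the primary one.

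The cost is a change of wording and a less favourable stated power. Recruitment, data collection and analysis do not change.
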